Preliminary data from another clinical study (i.e., global ACTT-1) demonstrated significant shortening of time to recovery for patients with moderate to severe COVID-19 when treated with remdesivir (median, 11 days, as compared with 15 days; rate ratio for recovery). In the case of patients with severe disease (88.2%; defined as requiring mechanical ventilation and/or supplementary oxygen) who were randomized to the remdesivir arm, 55.4% were no longer hospitalized by Day 15 post-treatment (versus 45.7% of patients treated with placebo) ([Beigel 2020](#)).

While preliminary findings support the use of remdesivir for patients who are hospitalized with COVID-19 and require supplemental oxygen therapy, the authors noted that given high mortality despite the use of remdesivir, it is clear that treatment with an antiviral drug alone is not likely to be sufficient to reduce mortality ([Beigel 2020](#)).

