## 4.4. STAGGERED COHORT ENROLLMENT

Each cohort will have a minimum of 3 patients enrolled. agenT-797 (Cohort 1) will be administered in the first patient, and treatment will be administered to the next patient 7 days after the last patient was administered agenT-797. Cohort 2 will be administered 14 days after the last patient was dosed in Cohort 1 and will follow the staggered dosing in Cohort 1 (every 7 days/patient). If patients tolerate low dose (Cohort 1) and intermediate dose (Cohort 2) treatment with agenT-797, Cohort 3 may be enrolled after 14 days.

An additional cohort in up to 15 patients will be evaluated:

- Cohort 4 – patients with moderate to severe ARDS secondary to SARS-CoV-2 or influenza, according to Berlin definition, who are on mechanical intubation

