### **4.5.1. Dose-Limiting Observation Period**

A minimum of 3 patients will be enrolled in each cohort, and the DLT observation period will be 14 days for each patient. Patients will continue to be monitored post-DLT period throughout the study. The totality of the safety data will be factored in by the SMC in the decision-making to move to enrollment of Cohort 2.

If a DLT occurs in 1 of the 3 patients during the DLT period, the cohort will be expanded to a total of 6 patients; if a DLT occurs in  $\geq 2$  patients in the total cohort of 6 patients, the MTD will be deemed to be exceeded, and that dose will not be escalated. The prior dose level will be evaluated to then proceed into the Expansion Cohort. The interval between patients in each cohort is at least 7 days with a 14-day interval between each cohort ([Section 4.4](#)).

The dose of agenT-797 will be escalated if none of the first 3 evaluable patients enrolled has a DLT based on SMC evaluations of data. If a cohort was expanded to include a total of 6 evaluable patients and no DLT occurs in the additional 3 patients, then the dose will be escalated based on the SMC evaluation of data.

After Amendment 7, the SMC will monitor safety on an ongoing basis.

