#### **4.5.6. Treatment and Evaluation Period**

Eligible patients will be treated with agenT-797 on Day 1. Assessments will be obtained through Day 32 or until discharge from hospital as outlined in the Schedule of Assessments in [Table 3](#).

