- a End-of-Hospitalization is defined as patient discharge from hospital and/or death. If a patient is discharged at Day 30, 30-day Follow-up will be the same as EOH. After discharge, a patient will enter Safety Follow-up period and the patient will be contacted by telephone 3 and 6 months after discharge regarding any SAEs and to confirm survival, as feasible. See [Sections 4.9 and 4.10](#).
- b In case of earlier discharge from the hospital, no visit is expected until 30-Day Follow-up.
- c Performed before infusion of agenT-797 on D1. These samples will be obtained at the time of the routine labs blood draws.
- d A complete examination, as feasible, will be performed at Screening and symptom-directed and medically indicated physical examinations are done thereafter.
- e Vital signs include body temperature, heart rate, respiratory rate, systolic and diastolic blood pressure and are assessed by physician or nurse. On the day of infusion of agenT-797 (D1), measurements will be 15 min prior to infusion, and 15 min, 30 min, 1h, 2h, 3h, and 4h postinfusion.
- f ECG to be performed at Screening, Day 1 predose and EOH, 30-Day Follow-up, and at other times as clinically indicated.
- g Only AEs associated with study procedures and/or leading to withdrawal and all SAEs will be collected prior to study drug infusion. Patients are monitored for toxicities following infusion. All other AEs, SAEs, and AESIs will be collected as per [Section 8](#) and as defined in the Safety Follow-up period ([Section 4.10](#)).
- h Hematology/coagulation/clinical chemistry: Complete blood count with automated and/or manual differential will be collected daily, as feasible. Coagulation: activated partial thromboplastin time and international normalized ratio. Clinical chemistry: includes but not limited to albumin, alkaline phosphatase, alanine aminotransferase, aspartate aminotransferase, blood urea nitrogen, urea, calcium, chloride, C-reactive protein, creatinine, glucose, lactate dehydrogenase, magnesium, phosphate/phosphorus, potassium, sodium, total bilirubin, direct and indirect bilirubin, total protein, and beta-2-microglobulin and will be collected daily, as feasible. All will be collected at EOH and at 30-Day Follow-up.
- i Urinalysis: pH, ketones, specific gravity, bilirubin, protein, blood, and glucose. Will be done at the days indicated and at EOH and at 30-Day Follow-up.

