#### **4.11. REPLACEMENT OF PATIENTS**

Patients are at any time free to withdraw from the study. Such patients will always be asked about the reason(s) and the presence of any AEs. AEs should be followed up as outlined in [Section 8.1.5](#). The Investigator may also elect to discontinue patients from the study, for example, to pursue a different treatment option. Reason(s) for discontinuation will be documented.

Patients who are withdrawn from the study but have completed treatment (infusion of agenT-797), are to be considered evaluable for DLT, and will not be replaced. Any patient who is withdrawn and is not considered evaluable for safety during Dose Escalation will be replaced to ensure a minimum number of evaluable patients.

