### 4.5 Analysis Sets

Three subject analysis sets are defined for the study analyses, as follows:

- **The All Subject Analysis Set** will include all patients who have completed informed consent, irrespective of the study treatment administered. This analysis set will be used for the disposition summary and the listing of study populations.
- **The Safety Analysis Set** will include all patients who received agenT-797. This analysis dataset will be used for safety analysis and all listings other than listings of subject disposition and study populations.
- **The Dose-Limiting Toxicity Analysis Set** will include all patients who either experienced a DLT within 28-day observation or completed study treatment and 28-

day observation for DLT without experiencing DLT. The DLT analysis set will be used for the analysis of DLT rates and for determining MTD.

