#### **4.11.5 Deaths, Serious Adverse Events, and Other Significant Adverse Events**

A serious AE (SAE) is an AE that fulfils one or more of the following criteria:

- Results in death.
- It is immediately life-threatening.
- It requires inpatient hospitalization or prolongation of existing hospitalization.
- It results in persistent or significant disability or incapacity, or substantial disruption of the ability to conduct normal life functions.
- Is or results in a congenital abnormality or birth defect.

Other significant AEs are those reported as leading to an intervention e.g. withdrawal from study, discontinuation of study treatment, introduction of concomitant medication, dose reduction.

CRS is a systemic inflammatory response characterized by a spectrum of severity, ranging from flu-like symptoms (i.e., fever, myalgia, nausea/vomiting), to hypotension, respiratory and renal failure, and uncontrolled coagulopathy. The onset of CRS can typically occur between 24 hours and 14 days after the completion of T cell administration. Therefore, after agenT-797 infusion, should CRS occur, it should be managed by the Investigator per institutional guidelines.

The American Society for Transplantation and Cellular Therapy (ASTCT) have published consensus guidelines for grading of CRS ([Lee 2019](#)). The ASTCT consensus grading guidelines are presented in

[Table 3](#) and align with management algorithms developed by Lee and colleagues ([Riegler 2019](#)), which are to be used as a guide for the Investigator in the assessment of CRS.

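### No scheduled assessment covers the rest of the DLT window after an early discharge, and three conflicting evaluability rules let the escalation decision and the reported DLT rate rest on different patients

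*Combined protocol and SAP*

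**What the plan says.** **The window.** Protocol 4.5.1 states that "the DLT observation period will be 14 days for each patient". The documents place much of the expected toxicity inside that period. SAP 4.11.5, like protocol 5.4.1.1, says: "The onset of CRS can typically occur between 24 hours and 14 days after the completion of T cell administration".

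**What is scheduled.** Protocol 4.5.6 states: "Assessments will be obtained through Day 32 or until discharge from hospital". In Table 3, footnote b is attached to the Day 14, 21, 28 and 32-to-EOH columns and reads: "In case of earlier discharge from the hospital, no visit is expected until 30-Day Follow-up". SAP Table 4 repeats it. The only scheduled telephone contacts are at 3 and 6 months after discharge, for SAEs and survival (protocol 4.10).

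**When the next dose may start.** Protocol 4.4: "Cohort 2 will be administered 14 days after the last patient was dosed in Cohort 1". Within a cohort, patients are dosed at least 7 days apart.

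**Who counts.** Protocol 4.11, repeated in SAP 3.9, says that patients withdrawn after completing the infusion "are to be considered evaluable for DLT, and will not be replaced". SAP 4.5 defines the DLT Analysis Set, which serves the DLT rates and the MTD, as patients who "experienced a DLT within 28-day observation or completed study treatment" and the 28-day observation without a DLT.

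**The concern.** A 3+3 rule decides on three patients at a time, and zero DLTs in three is enough to move on, subject to SMC review. Such a decision is only as good as the observation behind each zero. The plan waives the one scheduled visit near the end of the window for anyone who has already gone home, and 4.11 sets no minimum observation for a patient who withdraws after the infusion. Missing information can then enter the escalation decision as absence of toxicity, and the error always favours clearing the dose.

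The three evaluability rules add a second problem. The SMC can decide on one set of patients while the report gives the DLT rate and MTD on another, with nothing in the plan to explain the difference.

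**Working it through.** **1. The plan's own figure.** Protocol 9.2 allows up to 18 patients in Part 1. Three dose levels × 6 patients = 18, which reproduces it. The documents state no operating characteristics for the escalation rule.

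**2. The uncovered part of the window.** Take infusion as Day 1, so that 14 days after it is Day 15 (protocol 4.16.4 also labels +14 days as D15).
- Discharge on Day 7 leaves (15 − 7)/14 = 8/14 = 57% of the window with nothing scheduled.
- Discharge on Day 10 leaves (15 − 10)/14 = 5/14 = 36%.

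Footnote b is not attached to the Day 7 and Day 10 columns. For those days the gap comes from protocol 4.5.6.

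**3. Timing against the next cohort.** The next cohort can open on the last patient's Day 15. The Day 30 ± 2 visit falls on Days 28 to 32, which is 13 to 17 days later. That visit is itself not firmly placed: protocol 4.10 allows Day 30 or EOH, while the synopsis says 30 days after discharge. For a Day 7 discharge, these readings give Day 30, Day 7 or Day 37.

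**4. Different denominators.** With three patients at the minimum 7-day spacing, the earliest opening of the next cohort finds them 28, 21 and 14 days after infusion. If none has had a DLT:

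| Rule | Evaluable at that moment |
|---|---|
| Protocol 4.5.1, 14 days | 3 of 3, if all were observed |
| Protocol 4.11 / SAP 3.9, infusion completed (withdrawn patients) | any withdrawn patient counts at once |
| SAP 4.5, 28 days completed | at most 1 of 3 |

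**5. Size.** Let p be the true probability of a DLT in the window. Under protocol 4.5.1 a dose is escalated after 0 of 3, or after 1 of 3 followed by 0 of 3:

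P(escalate) = (1 − p)³ + 3p(1 − p)² × (1 − p)³

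At p = 1/3 this is 0.296 + 0.132 = 0.428.

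Suppose a share f of patients leaves early and a share u of their DLTs is never captured. Then p is replaced by p(1 − f·u). The documents give none of p, f or u; all three are assumptions.

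| Assumed f, u | p = 0.20 | p = 1/3 | p = 0.50 |
|---|---|---|---|
| full capture | 0.709 | 0.428 | 0.172 |
| 0.10, 0.25 | 0.719 | 0.444 | 0.186 |
| 0.25, 0.50 | 0.762 | 0.511 | 0.252 |
| 0.50, 0.50 | 0.814 | 0.600 | 0.351 |

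The increase runs from 0.719 − 0.709 = 1 point to 0.351 − 0.172 = 18 points.

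A concrete case: one patient in each three leaves on Day 7, DLT times are spread evenly, and nothing later is captured. That patient's visible risk is p × 6/14. P(escalate) goes from 0.709 to 0.788, from 0.428 to 0.550 and from 0.172 to 0.284 for the three values of p.

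For the rule that 4.11 does state, take one of three patients withdrawn straight after infusion, with nothing learned afterwards. At p = 1/3 the chance of seeing 0 of 3 goes from (2/3)³ = 0.296 to (2/3)² = 0.444.

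**The case against.** The strongest reply is that the plan does not abandon discharged patients. Footnote b waives a visit, not contact. Table 3 has adverse events collected throughout, and protocol 8.1.6 requires them to be recorded through 30 days. Re-admission counts as an SAE (8.1.2), and SAEs and AESIs go to the sponsor within 24 hours of awareness (8.1.10). A reader might infer that nobody observes these patients, or that post-discharge CRS or GVHD comes to light only at Day 30. The documents do not support that: a re-admission would be reported as soon as the site knew. What remains is that these are duties triggered by awareness, with no scheduled step that creates it. Some DLTs in 8.1.4 need not bring a patient back, and some depend on laboratory values, such as Grade 3 hematologic toxicity beyond 7 days. Daily laboratory tests end at discharge.

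A reader might also infer that an early-discharged patient is by rule DLT-evaluable. Section 4.11 speaks of withdrawn patients, whereas a discharged patient stays in follow-up. Extending the rule is plausible, since no other passage in the protocol defines DLT evaluability, but it is an inference. The SMC charter, which is a separate document, may deal with it.

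Nor does it follow that the reported DLT rate counts unobserved days as DLT-free. SAP 4.5 would leave out a DLT-free patient whose 28 days were not completed. That answers the point for the planned analysis of DLT rate and MTD, but it confirms the conflict with 4.5.1 and 4.11, on which escalation runs.

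Finally, Part 1 is marked as completed, and Cohort 4 enrols only intubated patients at the Cohort 3 dose. A non-intubated patient sent home in the first week cannot arise there. This stands, and it lowers the priority.

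**Conclusion.** The concern holds in a limited form. It is plain from the text that nothing is scheduled between a discharge inside the window and the 30-Day Follow-up, that the next cohort may open before that visit, and that protocol 4.5.1, protocol 4.11 with SAP 3.9, and SAP 4.5 do not agree on who is evaluable or for how long. The direction of any error in escalation is also clear: toward clearing a dose.

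The size is not known. The 1 to 18 points hold for assumed true DLT risks of 0.20 to 0.50, early-discharge shares of 10% to 50%, and 25% to 50% of those patients' DLTs missed; other inputs would give other figures. It is tempting to take the early-discharge share from protocol 2.1, where in a cited remdesivir trial "55.4% were no longer hospitalized by Day 15 post-treatment" on active treatment and 45.7% on placebo. Those patients needed ventilation and/or supplementary oxygen, a broader group than moderate to severe ARDS with intubation or high risk of it, so the figures cannot serve as this trial's rate.

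This is a correction of moderate priority. Its main present use is in how the Part 1 DLT rate and MTD, which support the dose in Cohort 4, are analysed and reported.

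**What to change.** 1. **Close the window.** In Table 3 footnote b, its copy in SAP Table 4, and protocol 4.10, add one safety contact at the end of the DLT window for any patient discharged earlier. It should cover all AEs, AESIs and the DLT criteria and obtain any laboratory results available, because a telephone call alone cannot settle laboratory-based DLTs. State one timing for the 30-Day Follow-up.
2. **One window, one rule.** Reconcile protocol 4.5.1, protocol 4.11, SAP 3.9 and SAP 4.5. The sponsor and SMC must decide the length of the window; the statistical need is that all four places carry the same one. A treated patient is then evaluable only if a DLT occurred or the end-of-window status was obtained. Otherwise the replacement provision already in 4.11 applies during Dose Escalation.
3. **Report the observation.** Tell the SMC at each review, and state in the study report, how many DLT-evaluable patients had the full window observed. Show the DLT rate with and without the others. This can be done now for the completed Part 1 cohorts.

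The cost is a wording amendment, an occasional call, an occasional replacement patient, and possibly a smaller DLT denominator.

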| Arterial blood gas                                                                    | X              | Daily monitoring/assessments as needed |   |   |   |   |        |                     |                     |                     |                        | X                | X          |
| Symptoms of ARDS p evaluation (Berlin definition) q             | X              | Daily monitoring/assessments as needed |   |   |   |   |        |                     |                     |                     |                        | X                | X          |
| SOFA score r                                                               | X              | Daily monitoring/assessments as needed |   |   |   |   |        |                     |                     |                     |                        | X                |            |
| Viral burden assessment (swab), or endotracheal suction as feasible (RT-PCR)          | X s | X                                      | X | X | X | X | X      | X                   | X                   | X                   |                        | X                |            |
| Viral shedding assessment as feasible                                                 |                | X                                      |   |   |   |   |        |                     |                     |                     |                        | X                |            |
| D-dimer, CPK, cardiac troponins, and ferritin                                         |                | Every 12h, as feasible                 |   |   |   |   |        |                     |                     |                     |                        | X                |            |

Abbreviations: AE: adverse events; AESI: adverse events of special interest; ARDS: acute respiratory distress syndrome; d: day(s); cfDNA: cell free DNA; CPK: creatine phosphokinase; CT: computed tomography; ECG: electrocardiogram; EOH: End-of-Hospitalization; F/U: Follow-up; HLA: human leukocyte antigen; h: hour (s); IL: interleukin; iNKT cells: invariant natural killer T cells; RT-PCR: reverse transcriptase polymerase chain reaction; SAE: serious adverse event; SOFA: sequential organ failure assessment; WOCBP: women of childbearing potential.

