### 8.1.4. Dose-Limiting Toxicity Criteria

The DLT observation period is defined as 14 days after infusion of agenT-797. The nature, frequency, time to onset, severity of toxicities, medical history, and concomitant medication, as well as the success of standard medical management, will be analyzed to determine if a given toxicity should be considered a DLT by the SMC per charter.

A DLT is defined as any of the following at least possibly related AEs graded using NCI-CTCAE v5.0:

- General:
  - Any Grade 4 or 5 toxicity
- Hematologic:
  - Any Grade 3 hematologic toxicity that lasts for more than 7 days despite treatment

- Non-hematologic:
  - Any Grade 3 non-hematologic toxicity that lasts for more than 72 hours despite adequate treatment
  - Exceptions: Grade 3 events with a different definition of duration that are considered DLTs are the following:
    - Grade 3 renal or hepatic toxicity that lasts 7 days or longer
    - Any Grade 3 or higher toxicity that is cardiac, respiratory, or neurologic of any duration
- Immune:
  - Any Grade 2 acute GVHD that requires steroid therapy for > 7 days or that has progression of clinical signs and symptoms after 3 days of steroids or that has partial response after 14 days of treatment, or GVHD Grade 3 or higher
  - Any **new** Grade 3 CRS lasting more than 72 hours and/or **new** Grade 4 CRS of any duration at least possibly related to agenT-797. For patients presenting with Grade 2 or 3 CRS at baseline, worsening of baseline CRS grade, judged as at least possibly related to agenT-797, and occurring within 4 hours of infusion ([Lee 2019](#))
  - Any clinically significant Grade 3 autoimmune disorder that lasts for more than 72 hours at Grade 3 despite adequate treatment or any Grade 4 autoimmune disorder of any duration

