##### **4.11.8.3 ECG**

A single, 12-lead ECG will be performed. The ECG will be evaluated by the Investigator as 'Normal', 'Abnormal, NCS' or 'Abnormal, CS'.

A summary of each ECG parameter will be generated.

A by-subject listing will be provided.

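### Patients still in hospital have no routine post-dose ECG in the 14-day DLT window, and footnote f omits the Day 28 ECG that the grid marks

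*Combined protocol and SAP*

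**What the plan says.** Protocol Table 3 and SAP Table 4 carry the same ECG row, with marks at Screening, Day 1, Day 28 ± 2, End-of-Hospitalization (EOH) and the 30-Day Follow-up. Footnote f to that row reads "ECG to be performed at Screening, Day 1 predose and EOH, 30-Day Follow-up, and at other times as clinically indicated". It makes the Day 1 ECG a pre-dose reading and does not mention Day 28. The Screening mark carries footnote c, "Performed before infusion of agenT-797 on D1".

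Protocol section 4.5.1 states that "the DLT observation period will be 14 days for each patient", and section 8.1.4 agrees: "The DLT observation period is defined as 14 days after infusion of agenT-797". Among at least possibly related events, section 8.1.4 counts this as a DLT: "Any Grade 3 or higher toxicity that is cardiac, respiratory, or neurologic of any duration". The Synopsis lists the 12-lead ECG among the safety measures, and section 5.3.3 asks sites to steer away from QT-prolonging drugs where they can.

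SAP section 4.11.8.3 promises: "A summary of each ECG parameter will be generated". It names no time points, although section 4.11.8 points to the schedule in Appendix 1. It plans no change from baseline for ECG, whereas section 4.11.8.2 does so for vital signs. SAP section 4.2 takes the last pre-treatment assessment as baseline.

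**The concern.** Safety is the primary objective, and a severe cardiac event counts as a DLT however brief it is. The ECG is the only scheduled measure that records QT interval and conduction, yet for a patient still in hospital both routine early readings come before the cells are given. ECG evidence within the DLT window then depends on someone seeing a reason to order one. Cohort 4 patients are all mechanically ventilated and may be unable to report symptoms, so an asymptomatic change could pass unrecorded.

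The ECG summary has a related weakness. For a patient who stays in hospital, the first routine post-dose value comes about four weeks after infusion, by which time critical illness and concomitant drugs are mixed with any effect of the product.

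Separately, grid and footnote disagree on Day 28. Sites could follow either, and the data at that visit would differ between sites.

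**Working it through.** The plan gives no figure to reproduce. The check is a count of scheduled ECGs, with infusion as Day 1.

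1. **Grid.** Table 3 has 13 columns: Screening, Days 1, 2, 4, 6, 7, 10, 14, 21 and 28, Day 32 to EOH, EOH, and 30-Day Follow-up. The ECG row has 13 cells, of which 5 are marked: Screening, Day 1, Day 28, EOH and 30-Day Follow-up. Days 2, 4, 6, 7, 10, 14 and 21 are blank.

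2. **Before or after dosing.** Footnote c places the Screening ECG before infusion, and footnote f places the Day 1 ECG before infusion. So 2 of 5 slots are pre-dose, and 5 − 2 = 3 are post-dose (Day 28, EOH, 30-Day Follow-up).

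3. **DLT window in the protocol.** 1 + 14 = Day 15, or Day 14 if Day 1 counts as the first day.

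4. **Next date-fixed ECG.** 28 − 2 = Day 26 to 28 + 2 = Day 30. That is 26 − 1 = 25 to 30 − 1 = 29 days after infusion, and 26 − 15 = 11 to 30 − 15 = 15 days after the window closes.

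5. **EOH.** "End-of-Hospitalization is defined as patient discharge from hospital and/or death", so this slot moves with the patient:
   - discharged by Day 15: one routine post-dose ECG, at discharge, inside the window;
   - discharged on Days 16 to 25: the first one is at discharge, after the window;
   - still in hospital from Day 26: the first one is at the Day 28 visit, if the grid governs.

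   For anyone still in hospital when the window closes, the count of routine post-dose ECGs inside it is 0.

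6. **If footnote f governs.** The Day 28 ECG disappears, and the next routine one is at EOH or the 30-Day Follow-up. On the timing in protocol section 4.10 (Day 30 ± 2), that follow-up falls on Days 28 to 32.

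7. **DLT window in the SAP.** SAP section 3.6 uses 14 days, but the DLT analysis set in SAP section 4.5 uses 28 days, which ends on 1 + 28 = Day 29. An ECG on Days 26 to 29 would then fall inside and one on Day 30 would not. There would still be no early post-dose reading.

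8. **Other cardiac information in the window.** Table 3 has a row for "D-dimer, CPK, cardiac troponins, and ferritin", every 12 hours as feasible. Footnote e gives six post-infusion vital-sign readings on Day 1 (15 and 30 minutes; 1, 2, 3 and 4 hours), and vital signs continue daily. Section 4.16.6 adds B-type natriuretic peptide and magnesium every 24 hours as feasible. Adverse events are collected continuously. None of these records QT interval or conduction.

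**The case against.** A reader might infer that ECG cannot inform the cardiac DLT at all, or that the Safety Monitoring Committee (SMC) has no systematic cardiac evidence. The documents do not support either reading. Footnote f itself allows further ECGs when clinically indicated, and a patient discharged within the window has an EOH ECG. The DLT is a graded adverse event that the SMC judges on nature, severity and course. On the protocol's general scale a Grade 3 event is incapacitating and a Grade 4 event calls for urgent intervention, so either would normally prompt an ECG. Troponins, vital signs, chemistry and adverse event review also run through the window. What remains is the silent change.

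A reader might also infer that unsound escalation decisions can still be corrected. Part 1 is marked completed, Cohort 4 uses the Cohort 3 cell dose, and the SMC reviews safety on an ongoing basis after Amendment 7. A change now can help only Cohort 4 and the report.

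Nor is one of the two pre-dose ECGs worthless. Under SAP section 4.2 the Day 1 pre-dose reading is the baseline, and Screening may be up to 4 days earlier (section 4.5.5). Dropping the later reading without care could leave an older baseline in unstable patients.

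Three further points stand in part:
- No adverse event of special interest in section 8.1.3 is cardiac, and the QT item is a precaution rather than evidence of a product effect. This lowers the urgency.
- SAP section 4.11.8.3 plans no change from baseline for ECG, so the missing early value breaks no stated analysis. It limits what the summary can show.
- A reading within 4 hours of infusion comes before the typical onset of cytokine release syndrome that section 5.4.1.1 gives (24 hours to 14 days).

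These points narrow the claim. They leave the count of zero and the Day 28 mismatch untouched.

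**Conclusion.** The point holds in a limited form. For a patient still in hospital, two ECGs are scheduled before infusion and none after it within the protocol's 14-day DLT window. The next date-fixed ECG comes 11 to 15 days after that window closes, and only if the grid rather than footnote f is followed. Silent ECG changes may be missed, and ECG ascertainment of cardiac DLTs depends on clinical indication. The ECG summary has no early routine post-dose value for these patients. The documents do not show that the cardiac DLT goes unassessed.

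The Day 28 mismatch is a plain contradiction in both documents, as is the 14-day against 28-day DLT window. Each must be reconciled.

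The conclusion rests on three assumptions:
- the SMC charter, which is not among the documents, adds no ECG;
- most Cohort 4 patients are still in hospital when the window closes, which is likely for ventilated patients but is not a figure in the plan;
- Cohort 4 is still enrolling. If it has closed, only the reconciliations and the reporting remain.

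**What to change.** - **Table 3 and SAP Table 4, footnotes c and f.** Keep one pre-infusion ECG as baseline, taken as close to infusion as feasible. Footnote c already places the Screening reading before the Day 1 infusion. Use the other pre-dose slot for an ECG inside the 4-hour post-infusion monitoring that section 5.1.2 already requires. The grid stays at five ECG slots.
- **Day 28.** Make footnote f and the grid agree, in both documents.
- **SAP section 4.11.8.3.** Report ECG parameters by time point, with change from the pre-dose ECG. State that later ECGs within the DLT window were obtained only when clinically indicated or at EOH.
- **DLT window.** Reconcile the 14 days in protocol sections 4.5.1 and 8.1.4 and SAP section 3.6 with the 28 days in SAP section 4.5.

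The cost is footnote edits in two tables and a few lines in the SAP. The price is one baseline ECG instead of two, possibly a slightly older one, and a single early reading leaves the rest of the 14 days to clinical indication. If enrolment has ended, the first item lapses. The report should then say that no routine post-dose ECG was scheduled in the DLT window for patients still in hospital.
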